### Data management {19}

For this pragmatic trial, we rely on routinely used data sources, such as the laboratory register, RR-TB treatment register, and the patient’s RR-TB treatment card. Data are imputed in Excel sheets, used for routine reporting since 2008 [8]. All source documents, as well as the consent forms, are archived at the RR-TB clinics. Routinely conducted quarterly supervision visits ensure data completeness. These visits are performed by the national RR-TB focal point, part of the National RR-TB Committee.

Data from these sources will be encoded in a national database in Excel (already is in place), and updated regularly by the research assistants, supervised by the principal investigator.

### Confidentiality {27}

Care and treatment are provided by NTP clinicians supported by DF staff. Patients will not be contacted by staff other than those who are also responsible for routine services. NTP clinicians at the RR-TB unit are responsible for ensuring appropriate storage of all study-related documentation.

All patient data will be pseudonymised in the database by means of a unique study number assigned to the participants. Treatment cards, lab results, and registers will only be accessible to NTP and DF staff involved in RR-TB care and their supervisors, all trained in confidentiality. The supervisors are also involved in the present RR-TB research.

### Plans for collection, laboratory evaluation and storage of biological specimens for genetic or molecular analysis in this trial/future use {33}

Baseline sputum samples are collected from all patients enrolled. Additional sputum samples are collected from patients with treatment failure or relapse. Sputum samples (outcome sample) will be stored in alcohol and sent to the supranational ITM laboratory in Antwerp to determine the resistance profile using Deeplex®-MycTB Deeplex for deep target sequencing (Deeplex; Genoscreen, Lille, France). Deeplex results obtained from the outcome sample will be compared with those obtained from the baseline sample to identify acquired resistance and to distinguish true failure or relapse (same strain) from reinfection (different strain). In case no Deeplex results are obtained, spoligotyping will be used to show the identity of the strain.

## Statistical methods

### Statistical methods for primary and secondary outcomes {20a}

#### Primary analysis

The proportion of patients with grade 3–5 AE will be compared between the experimental treatment arm and the control arm using a chi-square test (or exact Fisher test). A Cox regression model will be developed to measure the association between enrolment in either the experimental or control arm and the incidence of a grade 3–5 AE. All patients who started treatment will be included. The start of follow-up time will be the date of start of treatment. The end of follow-up time will be the date an AE was graded as grade 3–5. In patients without AE, the date of the end of treatment will be used if they were cured or completed treatment, or the date of the last visit in case the patient was lost to follow-up before ending the treatment, or the date of death in case the patient died during treatment.

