### Sample size {14}

A total of 230 patients will be included prospectively to compare treatment arms (115 patients for each) in order to be able to identify a correlation between the treatment arms and the occurrence of any grade 3–5 AE, assuming that the “hazard ratio” for developing a grade 3-5 AE is 3.2 times higher among patients in the experimental treatment arm (WHO all-oral regimen) compared to the control arm (STR that contains either a SLID or LZD; 5% vs 15%; with power 0.8, alpha 0.05).

Justification of assumptions :Of the 153 patients already treated according to the Niger RR-TB treatment strategy, with LZD replacing the SLID in the STR in case of ototoxicity and with monthly audiometry, 6 (3.9%) had an AE of degree 3–5 [15]. For the calculation of the sample size, a “conservative” estimate of 5% was used.Of the 33 patients treated with linezolid instead of the SLID in case of ototoxicity, 6 (18.2%) had grade 3–5 AE [15]. A “conservative” estimate of 15% was used to calculate the sample size.

In addition to the prospective treatment arms, a retrospective cohort of 255 patients enrolled on treatment between 2017 and April 2021 will be used during an interim analysis (see interim analysis), if characteristics known to affect the treatment outcome of the retrospective cohort are not significantly different from the prospective arms, and in case the proportion with a grade 3-5 adverse event is not significantly different between the retrospective cohort and those prospectively treated using the Niger RR-TB treatment strategy (SLID-containing regimen, with LZD replacing the SLID in case of ototoxicity).

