## Assignment of interventions: allocation

### Sequence generation {16a}

We randomise by monthly blocks. Depending of the month in which patients are diagnosed with RR-TB, patients with FQ-susceptible RR-TB are enrolled in either the experimental arm (WHO all-oral regimen, with BDQ and LZD) or control arm (STR that contains either a SLID or LZD) regimen. A coin toss determined which treatment arm is used for even (February, April, ...) or odd (January, March, ...) months for all RR-TB Units. The coin toss determined that odd months correspond to the experimental arm and even months to the control arm. The coin toss was done on 09 April 2021 by the principal investigator in the presence of the director of the NTP and all RR-TB units researchers to ensure that patients in the same clinic are treated with both the intervention during the trial study period. Following the coin toss, patients diagnosed in odd months are enrolled in the experimental arm, and those diagnosed in even months in the control arm (Fig. 1).

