#### Secondary analysis

By treatment arm, safety will be calculated as the proportion of all patients started on treatment and without any severe AE (safety endpoint). By treatment arm, treatment effectiveness will be calculated as the proportion of patients with a favourable outcome among all patients with either a favourable or unfavourable outcome. By treatment arm, adherence will be calculated as the proportion of patients who took at least 90% of the doses of RR-TB treatment. Cohorts will be compared using the chi-squared test. Bivariable and multivariable logistic regression models will be used to estimate the association between having an unfavourable treatment outcome and treatment arm (experimental vs control; the variable of interest), adjusted for potential confounding factors such as age, sex, HIV status, type of tuberculosis, bacillary load, extent of disease, body mass index (BMI) and initial resistance pattern. Factors associated (*p*-value <0.1) with having an unfavourable outcome will be included in the multivariable model, which then will be simplified by backwards elimination until all remaining factors have a *p*-value <0.05 (treatment arm, the variable of interest, will not be removed).

An additional Cox regression model will be developed to estimate the association between the variable “exposure to SLID vs LZD” and having a grade 3–5 AE probably or definitively related to either the SLID (ototoxicity) or LZD (haematological disorders, optic neuritis, neurological disorders). The variable “exposure to the injectable vs linezolid” will be treated as a time-dependent covariate, as described previously [15].

Analyses will be carried out with Stata software (version 16.1, College Station, TX).

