Our trial has important strengths. Findings will be generalisable to the Niger context, where RR-TB care is standardised, using the same procedures in all RR-TB treatment units, which all are participating in this trial. The design used is feasible for routine RR-TB care, using data collection and monitoring procedures in place for over a decade. As such we expect prospectively collected data to be reliable and complete. We anticipate that potential confounding bias will be overcome by random allocation with monthly blocks. An alternative design that would also have been feasible, e.g. a before-after cohort study, certainly would have resulted in a higher risk of confounding bias. To not extend the duration of the trial beyond what is justified, and considering that the RR-TB programme is very stable, we will also add already collected data on the RR-TB treatment strategy in the interim analysis, unless characteristics of the retrospective cohort differ from the prospective cohort.

The study design also has some weaknesses. Monthly block randomisation is still more vulnerable to confounding bias than individual randomisation. Therefore, using a multivariable regression, we will aim at correcting for any effect of known predictors of safety and effectiveness outcomes. Nevertheless, some residual confounding may still not be adjusted for. Secondly, the incidence of adverse events caused by e.g. second-line injectable drugs and/or linezolid varies by region. Therefore our safety findings may not be applicable to all settings. We hope that our creative study design will inform (RR-)TB trials in other countries, as updated WHO recommendations with a “very low certainty in the estimate of the effect” are translated to national policy and practice.

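### Arms are allocated by calendar month, but the primary and interim safety analyses name no month term, and the covariate correction promised for safety is described only for the secondary effectiveness model

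*Protocol article*

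**What the plan says.** **Allocation.** Sequence generation {16a} states "We randomise by monthly blocks". One coin toss settled the whole sequence: "The coin toss determined that odd months correspond to the experimental arm and even months to the control arm". The rule is the same in all four RR-TB units, so each unit gives both regimens in alternating months. The introduction and the abstract call month of diagnosis the stratifying variable.

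**Primary analysis.** The proportions with a grade 3–5 event are compared by chi-square or Fisher test. In addition, "A Cox regression model will be developed to measure the association between enrolment in either the experimental or control arm and the incidence" of such an event. Arm is the only model term named. Interim analyses {21b} applies the same Cox approach at 80 and 160 patients, and a significant arm difference ends enrolment.

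**Adjustment.** The Discussion concedes that month blocks leave more room for confounding than individual randomisation and answers that, "using a multivariable regression, we will aim at correcting for any effect of known predictors of safety and effectiveness outcomes". The section on Secondary analysis gives a logistic model for unfavourable treatment outcome with at least eight candidate factors. They are screened at p < 0.1 and entered in a model "which then will be simplified by backwards elimination until all remaining factors have a" p-value below 0.05, with arm always retained. The further Cox model in that section compares injectable with linezolid exposure, not the arms.

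**Sample size.** "A total of 230 patients will be included prospectively to compare treatment arms (115 patients for each"), on a hazard that "is 3.2 times higher among patients in the experimental treatment arm (WHO all-oral regimen) compared to the control arm" ("5% vs 15%; with power 0.8, alpha 0.05").

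**The concern.** When whole months are allocated, chance differences between months enter the arm comparison. A test that treats patients as individually allocated counts any such month-to-month variation as if it were precision, and its p-value is then too small. This reaches the interim looks as well, where significance stops enrolment.

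The second issue is confounding. The plan's stated safeguard for its weaker allocation scheme is regression adjustment. For the primary endpoint no such adjustment is described, although the interim section names BMI and co-morbidities as predictors of safety and uses them only to compare cohorts. Where adjustment is described, the rule selects on association with the outcome. A prognostic factor that is imbalanced between the arms but misses the p-value threshold is dropped, and the final interval for arm takes no account of the selection.

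**Working it through.** **1. Reproducing 230.** Schoenfeld's formula with 1:1 allocation, two-sided alpha 0.05 (sidedness is not stated), power 0.80 and hazard ratio 3.2:

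events = 4(1.96 + 0.84)² / (ln 3.2)² = 23.2.

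Dividing by the mean risk (0.05 + 0.15)/2 = 0.10 gives 232. Using control survival 0.95 and experimental survival 0.95^3.2 = 0.849 gives 230.5. The stated 230 is therefore consistent with a calculation for individually randomised patients, with no allowance for months. Expected events are 0.05 × 115 + 0.15 × 115 = 23, and the Cox power at 23 events is 79.6%.

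**2. Month size.** Three years of recruitment (Trial status) is about 36 months, so m = 230/36 = 6.39 patients per month, with about 18 months per arm.

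**3. Effect of ignoring months.** The documents give no intracluster correlation (ICC), so the range is assumed, and month effects are taken as independent of each other. Design effect DE = 1 + (m − 1) × ICC. The standard error is too small by 1 − 1/√DE. Size = 2[1 − Φ(1.96/√DE)]. Cox power uses 23/DE events.

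| ICC (assumed) | DE | SE too small by | True size of 5% test | Cox power |
|---|---|---|---|---|
| 0 | 1.00 | 0% | 5.0% | 79.6% |
| 0.01 | 1.05 | 3% | 5.6% | 77.5% |
| 0.02 | 1.11 | 5% | 6.3% | 75.5% |
| 0.05 | 1.27 | 11% | 8.2% | 69.7% |

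A simulation of the unadjusted chi-square test (36 alternating months, 230 patients, 10% risk, 20,000 runs) gave sizes of 4.9%, 5.7%, 6.4% and 8.7% for the same four ICCs. A month-robust test stayed at about 5% throughout.

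**4. Two conditions that shrink the effect.**
- *Persistence.* Alternating arms every month spreads slow variation almost evenly over both arms. At ICC 0.05, simulated size falls from 8.7% with independent months to 6.3%, 5.7% and 4.9% at month-to-month autocorrelations of 0.5, 0.8 and 0.95 (assumed values).
- *Scope.* If correlation acts only within a unit in a given month, there are 4 × 36 = 144 cells of about 1.6 patients. DE is then only 1.03 at ICC 0.05 with equal cells, and size is 5.3%.

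**5. Room for covariates.**
- *Safety.* With 23 events, arm plus one covariate leaves 23/2 = 11.5 events per parameter, and arm plus two leaves 23/3 = 7.7.
- *Effectiveness.* If the 83% relapse-free cure reported for Niger applied to both arms, there would be 0.17 × 230 = 39 unfavourable outcomes. If the 73% end-of-treatment success quoted for the all-oral regimen applied to the experimental arm, there would be 0.17 × 115 + 0.27 × 115 = 51. Against eight candidates that is about 5 to 6 per candidate, before the planned exclusions.

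**6. Interim looks.** At 6.39 patients per month, 80 patients span about 12 to 13 prospective months, and 160 span about 25.

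**The case against.** The strongest reply is that no harm is shown. Without an ICC the plan's standard errors may be correct, and the usual suspects (staffing, season, drug supply) tend to last longer than a month, so monthly alternation largely balances them. This stands, and it is why the inflation is stated as conditional. Material inflation needs shocks that are confined to single months and shared across the units. The balancing argument covers the prospective months only. The retrospective patients who may be added at the interim looks were all treated under the control strategy.

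Three stronger readings are tempting, and the documents do not support them.
- *The standard errors are simply wrong.* They are too small only if outcomes correlate within months; at ICC 0 nothing changes.
- *Leaving out the unit also understates error.* Every unit gives both regimens, so unit is crossed with arm. Omitting it mainly loses some precision.
- *The primary Cox model is fixed as unadjusted.* Saying that a model will be developed does not exclude covariates, and an analysis plan not shown may list them. What can be faulted is the mismatch within the article: the correction is promised for safety and effectiveness, but candidate factors and a selection rule are given for effectiveness alone.

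It is also fair to say that p-value selection touches only a secondary model that always keeps arm, under an objective worded as describing effectiveness and finding predictors. That lowers the stakes, but the same model is where the plan adjusts the arm comparison for confounding.

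**Conclusion.** The point holds as a low-cost improvement. As written, the primary and interim tests are not protected against within-month correlation, although month is the unit of allocation. For an assumed ICC of 0 to 0.05 with independent months, true size runs from about 5% to about 8% and standard errors are 0% to 11% too small. Slowly varying month effects, or correlation limited to unit-months, would bring this close to nominal. Separately, and without any ICC assumption, the safety adjustment that the Discussion relies on is not described for the primary endpoint, and the adjustment that is described can discard a real confounder.

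**What to change.** **Primary analysis.** Specify a Cox model with arm plus one or two pre-named baseline safety predictors already collected, for example BMI and HIV status or another co-morbidity. Cluster the standard errors on month of diagnosis with a small-cluster correction, and show the unadjusted result alongside. Stratifying by unit is optional and serves precision only.

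**Interim looks.** Use the same inference. The small-cluster correction matters most at 80 patients, where there are only about 12 to 13 prospective months.

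**Effectiveness model.** Replace the screen and backward elimination with a short fixed list, for example age, HIV status, BMI and bacillary load, kept whatever the p-values, with the same clustering by month.

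**Cost.** A few lines of text and standard Stata options, with no new data. Intervals widen slightly if month-level correlation exists, and events per parameter in the safety model are few, hence the limit of two covariates. With a single coin toss followed by strict alternation, these changes do not fully restore randomisation-based inference, and the report should say so.

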#### Secondary analysis

By treatment arm, safety will be calculated as the proportion of all patients started on treatment and without any severe AE (safety endpoint). By treatment arm, treatment effectiveness will be calculated as the proportion of patients with a favourable outcome among all patients with either a favourable or unfavourable outcome. By treatment arm, adherence will be calculated as the proportion of patients who took at least 90% of the doses of RR-TB treatment. Cohorts will be compared using the chi-squared test. Bivariable and multivariable logistic regression models will be used to estimate the association between having an unfavourable treatment outcome and treatment arm (experimental vs control; the variable of interest), adjusted for potential confounding factors such as age, sex, HIV status, type of tuberculosis, bacillary load, extent of disease, body mass index (BMI) and initial resistance pattern. Factors associated (*p*-value <0.1) with having an unfavourable outcome will be included in the multivariable model, which then will be simplified by backwards elimination until all remaining factors have a *p*-value <0.05 (treatment arm, the variable of interest, will not be removed).

An additional Cox regression model will be developed to estimate the association between the variable “exposure to SLID vs LZD” and having a grade 3–5 AE probably or definitively related to either the SLID (ototoxicity) or LZD (haematological disorders, optic neuritis, neurological disorders). The variable “exposure to the injectable vs linezolid” will be treated as a time-dependent covariate, as described previously [15].

Analyses will be carried out with Stata software (version 16.1, College Station, TX).

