## Introduction

### Background and rationale {6a}

The treatment of rifampicin-resistant tuberculosis (RR-TB), TB resistant to the most powerful anti-TB drug, requires a more complex regimen than the treatment of rifampicin-susceptible TB and more frequently causes severe adverse drug reactions. Until 2016, 18–24 months long and poorly tolerated RR-TB treatment regimens were recommended [1]. These regimens were individualised, thus not standardised, and resulted in not much more than 60% treatment success [2].

In 2016, WHO recommended a standardised short treatment regimen (STR) for patients not yet exposed to second-line drugs and without resistance to the main components of this STR [3]. This STR had achieved a high cure rate (over 80%) among RR-TB patients in multiple programmatic settings [4–8]. However, this STR included a second-line injectable drug (SLID; amikacin, kanamycin or capreomycin), known for causing severe hearing loss as main adverse drug reaction [9]. A review showed that SLID had to be discontinued in about 10% of patients due to adverse events (AE) [10].

The increasing availability of novel drugs, such as bedaquiline (BDQ) and delamanid (DLM), and repurposed drug, such as linezolid (LZD) and clofazimine (CFZ), allow the designing of potent RR-TB treatment regimens solely relying on oral drugs. The 2019 WHO RR-TB treatment guidelines recommend replacing the STR’s SLID with bedaquiline [11]. WHO also recommends research on STR using both BDQ and LZD in patients who have not yet taken second-line drugs for more than one month and for whom fluoroquinolone resistance has been ruled out [12]. This WHO BDQ/LZD-containing all-oral STR resulted in 73% end-of-treatment success in South Africa [13, 14], considerably lower than 83% relapse-free cure obtained with the RR-TB treatment strategy used in Niger [8].

In Niger, patients are treated with a SLID-containing STR. The STR’s SLID is replaced by LZD in patients with contraindications for SLID, mainly ototoxicity. Audiometry is done at baseline and on a monthly basis during treatment. As any audiometry abnormality serves as an indication for switching to LZD, not a single RR-TB patient developed severe hearing loss since 2017 [15]. BDQ is safeguarded for the rare patients with treatment failure or relapse after a first STR, leaving not a single patient without a potentially successful retreatment option [8].

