## Interventions

### Explanation for the choice of comparators {6b} and intervention description {11a}

The control arm relies on the Niger RR-TB treatment strategy. It relies on the national 9–11- month standard RR-TB STR, which includes moxifloxacin (MFX), CFZ, ethambutol (E), and pyrazinamide (Z) throughout, supplemented by a SLID (amikacin), prothionamide (PTO) and high-dose isoniazid (Hh; 10mg/kg) during the first 4 months (6 months if delayed conversion on smear microscopy at treatment month 4). The SLID is replaced with LZD in case of any hearing disturbance detected on audiometry (4-6 SLID-Hh-PTO-MFX-CFZ-E-Z/5 MFX-CFZ-E-Z, with LZD replacing the SLID in case of any hearing disturbance detected on audiometry, at baseline or during treatment).

In this control arm, the STR uses fluoroquinolone (moxifloxacin) as core drug, with both high bactericidal and sterilising activity. The SLID (or LZD if it replaces SLID) provides early bactericidal activity, and the other drugs add bactericidal or sterilising activity [16].

The experimental arm uses the WHO all-oral regimen, which contains LZD, high-dose isoniazid, prothionamide, high-dose levofloxacin (LFXh), BDQ, CFZ and pyrazinamide for 4 months (6 months if delayed conversion on smear microscopy at treatment month 4), followed by 5 months of treatment with high-dose levofloxacin, BDQ, CFZ and pyrazinamide (4-6 LZD-Hh-PTO-LFXh-BDQ-CFZ-Z/5 LFXh-BDQ-CFZ-Z).

BDQ and fluoroquinolone (levofloxacin) are used as core drugs, thus with high bactericidal and sterilising power. LZD, with good early bactericidal activity, protects BDQ and fluoroquinolone from the acquisition of resistance. The other drugs add bactericidal or sterilising activity [16].

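### The secondary SLID-versus-LZD Cox model will more likely than not have no qualifying events in SLID time, and a standard fit would then give no finite hazard ratio or upper limit

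*Protocol article*

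**What the plan says.** The Secondary analysis section of the protocol begins the relevant sentence with "An additional Cox regression model will be developed to estimate the association between the variable". The variable is exposure to the injectable or to linezolid, with those two values, treated as time-dependent in the way a cited earlier study did. The outcome is a grade 3–5 AE probably or definitely related to one of the two drugs: ototoxicity for the SLID; haematological disorders, optic neuritis or neurological disorders for LZD.

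Three other sections bear on how many events this model can expect.

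- **Background and rationale {6a}**: because any audiometry abnormality triggers the change to LZD, "not a single RR-TB patient developed severe hearing loss since 2017". The Discussion repeats this.
- **Sample size {14}**: "Of the 153 patients already treated according to the Niger RR-TB treatment strategy", 6 (3.9%) had a grade 3–5 AE. From the same cited source, "Of the 33 patients treated with linezolid instead of the SLID in case of ototoxicity, 6 (18.2"%) had one.
- **Intervention description {11a}**: the control regimen is "supplemented by a SLID (amikacin), prothionamide (PTO) and high-dose isoniazid (Hh; 10mg/kg) during the first 4 months" (6 months if smear conversion is delayed), followed by 5 months without the SLID. LZD in the experimental arm is likewise confined to the intensive phase.

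**The concern.** The model's stated purpose is to estimate an association. In SLID time the only event that can count is severe ototoxicity, and the control strategy is built to end SLID time before ototoxicity becomes severe. The named method, the narrow event definition and the documented history therefore pull against each other.

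If every qualifying event falls in LZD time, the Cox partial likelihood keeps rising as the log hazard ratio increases and has no maximum. The report would then contain no finite hazard ratio and no upper limit, and its Wald statistic would mean nothing. A replacement would have to be chosen after the data are seen, by a researcher and statistician who, under the blinding section, know the regimens. This is the planned model that separates the two drugs directly, so the choice should be made beforehand.

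A smaller point concerns the exposure variable. It is described with two values, while neither drug is scheduled after the intensive phase.

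**Working it through.** **1. The plan's own figure.** The protocol gives no event count or power for this model. Its only calculation is for the primary comparison: "A total of 230 patients will be included prospectively to compare treatment arms (115 patients for each"), with "5% vs 15%; with power 0.8, alpha 0.05" and a hazard ratio of 3.2.
- Implied hazard ratio: ln(0.85)/ln(0.95) = 3.17, stated as 3.2.
- Schoenfeld events, two-sided: 4 × (1.960 + 0.842)² / (ln 3.2)² = 23.2.
- Mean event probability: (0.05 + 0.15)/2 = 0.10, so N = 23.2/0.10 = 232, against 230 stated.

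The stated size is reproduced and is not in question.

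**2. SLID-only history.**
- Patients: 153 − 33 = 120. Severe AEs: 6 − 6 = 0.
- This treats the 33 as part of the 153. That is the natural reading, since both counts come from one source and the 153 are described as including patients whose SLID was replaced.
- One-sided 95% upper limit from 0 of 120: 1 − 0.05^(1/120) = 2.5% per patient.

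**3. Patients exposed to SLID in the trial.** Scaled to 115 control patients, 115 × 33/153 ≈ 25 receive LZD and about 90 stay on SLID. The number with SLID time therefore lies between 90 and 115.

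**4. Predictive chance of zero SLID events.** With a uniform prior, P(0 of m | 0 of n) = (n + 1)/(n + m + 1); for example 121/211 = 0.57. The Jeffreys prior uses the beta-binomial with parameters 0.5 and n + 0.5. History is taken as 0 of 120 (SLID only) or 0 of 153 (everyone, from the hearing-loss statement).

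| History | m | Uniform | Jeffreys |
|---|---|---|---|
| 0/120 | 90 | 0.57 | 0.76 |
| 0/120 | 115 | 0.51 | 0.71 |
| 0/153 | 90 | 0.63 | 0.79 |
| 0/153 | 115 | 0.57 | 0.76 |

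The range is 51–79%.

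**5. Sensitivity to the true risk.**
- Risk 0.25%, 90 patients: 0.9975^90 = 0.80.
- Risk 1%, 115 patients: 0.99^115 = 0.31.
- Risk at the 2.5% upper limit: 0.05^(90/120) = 0.11 for 90 patients, and 0.05^(115/120) = 0.06 for 115.
- Planning rates: 115 × 5% = 5.75 control events, less 24.8 × 15% = 3.72 in patients on LZD, leaves 2.03; exp(−2.03) = 0.13. These rates cover any grade 3–5 AE and are called conservative, so they overstate the narrower drug-related endpoint.

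**6. What the fit returns with zero SLID events.** The simulation had 115 patients on LZD from the start, 115 controls of whom 25 switch during months 0–4, no events in SLID time, a 9-month horizon and 300 runs per LZD risk. Medians:

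| LZD risk | Events | Cox estimate | LR p | Score p | Profile lower limit | Firth HR (interval) |
|---|---|---|---|---|---|---|
| 10% | 13 | diverges | 1.2e-4 | 1.6e-3 | 4.9 | 21 (2.8 to 2,644) |
| 15% | 20 | diverges | 1.8e-6 | 8.7e-5 | 7.7 | 32 (4.4 to 3,944) |
| 18.2% | 24 | diverges | 1.5e-7 | 1.6e-5 | 9.4 | 38 (5.4 to 4,770) |

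The estimate diverged in every run. The tests and the lower limit did not fail.

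**7. Time on neither drug.** If follow-up runs to the end of treatment, as in the primary analysis, the scheduled off-drug share is 5/9 = 56% of a 9-month course and 5/11 = 45% of an 11-month course.

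**The case against.** The best counter-argument is that the model still answers whether LZD carries more severe drug-related toxicity. The protocol does not say that inference will be by Wald statistics. As step 6 shows, likelihood-ratio and score tests work with zero events in one group and would detect a large LZD excess, and a lower limit is available. This stands. A reader might infer that no p-value or interval could be obtained; that is not so. What is lost is the point estimate, the upper limit and Wald output.

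A second argument is that zero SLID events is not what the plan predicts. This also stands in part. The protocol nowhere states such an expectation. The 0 of 120 is a subtraction, and the timing of the six events is not given. Severe hearing loss is not tied explicitly to grades 3–5, which Table 2 defines by limitation of activity and need for intervention. At the upper end of what the history allows, zero events would be unlikely (6–11%).

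Third, it is tempting to say that off-drug months must be forced into the SLID or the LZD group. The documents do not support this. The coding is referred to a cited study that is not available here, and the end of follow-up for this model is not restated. Nor does 45–56% of time measure bias, because Cox risk sets are formed only at event times.

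Finally, methods for sparse events are often left to an analysis plan, and this is a condensed article. Silence on that detail would be no finding. The point survives because the article itself names a method and an event definition that, on its own history, probably cannot yield the estimate sought.

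**Conclusion.** The concern holds in a limited form. On the protocol's history, the chance of no qualifying event in SLID time is roughly 50–80%. The standard Cox hazard ratio and its upper limit would then be infinite and Wald inference unusable, while likelihood-ratio and score p-values and a profile-likelihood lower limit would remain.

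This rests on three assumptions: the 33 LZD patients are a subset of the 153; the six events arose in LZD time; and severe hearing loss corresponds to grade 3–5 ototoxicity. More likely than not is the right strength; near-certainty is not.

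How off-drug time is coded is a minor point of clarity, not a demonstrated error. The model is secondary and serves none of the listed objectives or endpoints. The primary comparison, the 230-patient sample size and the interim rules do not depend on it. The change is worth making because it is nearly free and is better settled before the data are seen.

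**What to change.** In the Secondary analysis section, replace the unqualified Cox fit with one of the following.

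- **Penalised model:** Firth-penalised Cox regression with profile-likelihood intervals and a likelihood-ratio test, keeping the time-dependent exposure.
- **Rates by exposure:** severe drug-related events per person-month on SLID and on LZD, each with an exact Poisson interval, and an exact (mid-P) comparison. With zero SLID events the rate still has an upper limit. For example, 90 patients × 4 months = 360 person-months gives −ln(0.025)/360 = 3.69/360, about 1.0 per 100 person-months. This option treats rates as constant over the exposure period.

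As a minor addition, say how time after the intensive phase enters the exposure variable, for instance a third state for neither drug, or time on drug plus a carry-over window fixed in advance.

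The cost is a few lines of text and code, with no new data, since AEs are already recorded by type, degree and month. The downside is wide intervals: in the simulation the Firth interval at a 15% LZD risk ran from about 4 to about 3,900. That reflects how little the SLID side can contribute.
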